### Primary and secondary efficacy endpoints

The primary and secondary efficacy endpoints are summarised in box 2. The primary endpoint consists of total hospitalisations for heart failure (first and recurrent) and cardiovascular death. Hospitalisations for heart failure include events where heart failure was the primary or a major contributory reason for admission (with a minimum of an overnight stay). For instance, a patient admitted with a primary diagnosis of atrial fibrillation or myocardial ischaemia who had, at the time of admission, worsening breathlessness and/or increasing peripheral oedema requiring treatment with a loop diuretic, would count as a primary endpoint. To reduce double counting of events, cardiovascular death during a hospitalisation for heart failure and readmissions for heart failure occurring on the same day as discharge from a previous heart failure admission are not counted as recurrent events.

Box 2Primary and secondary endpointsPrimary endpointCardiovascular (CV) mortality or hospitalisation for worsening heart failure (analysis will include recurrent hospitalisations)Secondary endpoints
Secondary efficacy
Hospitalisation for worsening heart failure (recurrent events).CV hospitalisation (first event)CV death or hospitalisation for heart failure analysed as time to first event.Overall Score from Minnesota Living with Heart Failure at 4 months.Cardiovascular mortality.Overall EQ-5D visual analogue score (VAS) at 4 months.Overall EQ-5D index at 4 months.CV mortality or hospitalisation (first event) for major CV event including: stroke, myocardial infarction and heart failure.All-cause mortality.All-cause hospitalisation (first event).Combined all-cause mortality or first all-cause unplanned hospitalisation.Physical domain of Minnesota Living With Heart Failure at 4 months.Physical domain of Minnesota Living With Heart Failure at 20 months.Overall EQ-5D VAS at 20 months.Overall EQ-5D index at 20 months.Overall Score from Minnesota Living with Heart Failure at 20 months.Days dead or hospitalised at 3 years.Quality-adjusted days alive and out of hospital at 12 months.Six minute walk test at 4 months.Six minute walk test at 20 months.
Secondary safety
Death due to infection.Hospitalisation primarily for infection.

### Safety assessments

Investigators are asked to report serious adverse events (SAEs). This does not include routine treatment or monitoring of heart failure; elective or preplanned treatment for a pre-existing non-cardiac condition; any admission for general care without deterioration in health; and treatment on an emergency, outpatient basis for an event not fulfilling the definition of an SAE.

All emergency day-case treatments for heart failure or elective percutaneous coronary intervention or cardiac device insertion are to be recorded as SAEs. Investigators are expected to report all blood transfusions and any important bleeding event, even if it does not require hospitalisation or was not life threatening. Death due to infection and hospitalisation due to infection are secondary safety endpoints.

Record linkage to national databases of deaths, hospital admissions and incident cancers is planned at the end of the trial in England and Scotland and for deaths in Wales to ensure complete reporting of events.

### Sample size and statistical analysis

Sample size calculations based on recurrent event analyses are difficult (additional sample size calculations are given in online supplemental appendix 2). Conservatively, we based our calculations on a time to first event analysis in a Cox proportional hazards model. We expected to recruit half the participants during a hospitalisation. The anticipated first primary endpoint rate in the control group was 60% at 3 years. We estimated that 570 participants per group (yielding 631 first primary outcomes) would provide 80% power to detect an HR of 0.8 at the 5% significance level. Allowing for non-cardiovascular mortality and some withdrawals of consent for follow-up, we intended to recruit 650 patients per group.

10.1136/heartjnl-2022-321304.supp2Supplementary data

The Independent Data Monitoring Committee (IDMC) conducted interim analyses of the primary endpoint when approximately 50% and 70% of the target number of first primary endpoints had been reached, requiring p<0.001 to recommend early stopping.

The primary endpoint will be analysed by the method of Lin *et al*
9 including the randomised treatment group and recruitment context as covariates. The estimated rate ratio, 95% CI and p value will be reported, with accumulated events displayed using the method of Ghosh and Lin.^10^

Secondary endpoints will be analysed hierarchically in the order shown in box 2, if the primary analysis is significant at the 5% level. Endpoints in the list will continue to be tested until one fails to reach 5% significance. Power calculations have been carried out for the first four secondary endpoints (online supplemental appendix 2).

Secondary endpoints involving recurrent events will be analysed as for the primary endpoint. Time to first event outcomes will be analysed using Cox proportional hazards models including treatment effect and recruitment context, with the treatment effect HR and 95% CIs estimated with associated p values using the Wald statistic and treatment groups compared graphically using cumulative incidence functions.

QoL scores and 6 min walk tests results at 4 and 20 months will be compared between randomised treatment groups using analysis of covariance, with treatment group and stratification variable as covariates.

Subgroup analyses will be carried out for the primary endpoint, analysed as a recurrent event and then separately as time-to-first event.

A formal Statistical Analysis Plan will be finalised before trial database lock.

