### Randomisation

Consenting and eligible patients were randomised with equal probability to the two treatment arms, stratifying by recruitment context (in hospital, recently discharged or ambulatory with elevated natriuretic peptide) and trial site, using a web-based system based on randomised, permuted blocks of variable size.

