### Modifications to sample size

In practice, we recruited mainly outpatients who had a lower rate of events; recruitment was slower than expected, especially during the COVID-19 pandemic, which also may have reduced cardiovascular admissions, resulting in a lower event rate for the primary endpoint. This, in combination with likely patient and investigator fatigue, led the Trial Steering Committee (TSC) to revise the power calculation for the trial. Assuming an HR of 0.75, as in AFFIRM-AHF trial,^11^ we calculated that 379 first primary endpoints would now provide 80% power at the 5% significance level.

Analyses based on patients randomised until the end of March 2020 with a censoring date of 30 September 2020 will be carried out to assess the impact of the COVID-19 pandemic on the results.

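### The primary rate model adjusts only for recruitment context and omits baseline values known from eligibility: a modest loss of efficiency, not of validity

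*Protocol article*

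**What the plan says.** All under Sample size and statistical analysis unless stated.

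- The primary endpoint (total heart failure hospitalisations and cardiovascular death) is analysed with a proportional-rates model for recurrent events, "including the randomised treatment group and recruitment context as covariates". Recurrent-event secondary endpoints follow the same model.
- Time-to-first-event endpoints use "Cox proportional hazards models including treatment effect and recruitment context".
- Randomisation is 1:1, "stratifying by recruitment context (in hospital, recently discharged or ambulatory with elevated natriuretic peptide) and trial site" (Randomisation). Context is therefore a stratification factor with three levels.
- Box 1 and the text after it in Trial design set limits on age, LVEF, NYHA class, haemoglobin and eGFR that every participant must meet. A natriuretic peptide value is a qualifying criterion for outpatients only.
- The original design, on a time-to-first-event basis, took 631 first events, which "would provide 80% power to detect an HR of 0.8 at the 5% significance level". Modifications to sample size lowers the target to 379 first events by moving the assumed hazard ratio to 0.75. It explains that "we recruited mainly outpatients who had a lower rate of events".
- The analysis plan is to be finalised before database lock. The article mentions no adjusted supportive analysis.

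**The concern.** The covariate lists are stated, not deferred, and recruitment context is the only baseline term in them. If age, LVEF, NYHA class, haemoglobin and eGFR predict events within a recruitment context, the planned primary model leaves explainable variation between patients in the robust SE. The confidence interval is then wider, and the primary test weaker, than the data in hand allow.

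Two features of the plan make efficiency worth having. The event target fell from 631 to 379. The secondary endpoints are tested in hierarchy only if the primary result reaches 5% significance, so power lost in that one test is lost for the whole list.

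**Working it through.** **1. The plan's own figures.** Schoenfeld formula, 1:1 allocation, 80% power, 5% taken as two-sided (the sidedness is not stated): events = 4(1.960 + 0.842)² / (ln HR)².

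- HR 0.80: 31.40 / 0.04979 = 631. Stated: 631.
- HR 0.75: 31.40 / 0.08276 = 379.4, or 380 rounded up. Stated: 379.
- 570 per group, 60% control risk, HR 0.80: treated risk = 1 − 0.4^0.8 = 0.520; events = 570 × (0.600 + 0.520) = 638. Stated: 631, within 3%.
- 379 events if HR is 0.80: power = Φ(√379/2 × 0.2231 − 1.960) = Φ(0.21) = 58%.

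The sample-size figures reproduce and are not in question. The last line shows how little margin there is if the effect is nearer the original assumption.

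**2. Why adjustment helps the rate model.** Roughly, the squared robust SE of the log rate ratio is (4/N)(1/μ + V). Here μ is the mean event count per participant, and V is the squared coefficient of variation of risk that the model leaves unexplained. Adjustment lowers V only, so the gain is bounded. Without a terminal event, a covariate independent of treatment leaves a log-linear rate ratio unchanged.

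**3. Size in the primary model.** Prognostic strength, frailty, follow-up and death rates are all assumptions. SD is that of the predictor on the log-rate scale; each entry is the percentage cut in SE.

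| Simulation | SD 0.3 | SD 0.5 | SD 0.7 |
|---|---|---|---|
| A. N=1300, gamma frailty, no context term, no death, 2500 runs | 2% | 5% | 10% |
| B. N=1140, context (15/20/65%) in both models, no death, 3000 runs | 2% | 5% | 10% |
| C. As B, death ends follow-up; CV death counted, unaffected by treatment | 1% | 4% | 7% |
| D. N=1300, yearly rates 0.17 (hospitalisation), 0.06 (CV death), 0.04 (other death), shared risk, 400 runs | 1% | 2% | 4% |

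- A, as an example: SE 0.1103→0.1083, 0.1140→0.1082 and 0.1220→0.1094.
- Power in B: 75→76%, 69→74%, 61→70%. Power in C: 63→64%, 59→62%, 53→59%. Gains in D: about 0.5 to 5 points, with Monte Carlo error of about 2 points.
- A further repeat with context in both models gave 2/5/10% without death and 1/4/6% with death.
- A, B and C used a Poisson model with robust SE in place of the planned model. The planned model itself, with context in both fits, log-normal frailty, N=1140 and no death, gave SE 0.105→0.101 at SD 0.4 (4%) and 0.115→0.102 at SD 0.7 (11%). Power was 77→81% and 69→79%.
- Rate ratio: the same to within 0.001 in B and C; 0.768 against 0.765 in D.
- Type I error in B and C: 4.8–5.8% unadjusted, 4.9–5.2% adjusted.

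The absolute power levels reflect the assumed inputs and do not estimate the trial's power. Only the differences matter here.

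**4. Cox models.** The SE is set mainly by the event count: 2/√379 = 0.103. In simulation it stayed at 0.104 (SD 0.4) and 0.103 (SD 0.7) with or without adjustment. The log hazard ratio moved from −0.246 to −0.255 and from −0.236 to −0.255, and power went from 67 to 68% and from 65 to 71%. The gain comes from undoing attenuation towards 1, and the adjusted hazard ratio is conditional on the covariates.

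**The case against.** The strongest reply is that nothing here is wrong. Adjusting for a stratification factor is conventional, type I error is sound, and the sample-size figures reproduce. The analysis plan is not shown and could add covariates. No passage says how strongly the five values predict events, and eligibility narrows them: LVEF is at most 45% and may be two years old, NYHA class is II to IV, and haemoglobin is bounded below and above. An SD near 0.3, with a gain of 1% to 2% in SE, is a live possibility. Simulations that ignore death overstate the gain. Changing the primary model late in an open-label trial, after two interim analyses, could look data-driven.

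Most of this stands and limits the claim to efficiency. It does not remove the point, because the article names its covariates instead of leaving them open, and the gain persists with context in both models and with death included.

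A reader might go further in two ways that the document does not support.

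- **That recruitment context separates risk poorly because mainly outpatients were enrolled.** The same sentence says that outpatients had fewer events, so context is prognostic and already takes part of the gain.
- **That the omitted values are strong predictors.** This is an assumption. Natriuretic peptide, moreover, is not shown to be available for everyone.

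**Conclusion.** The point holds as a modest, avoidable loss of efficiency in the primary and recurrent-event rate models. For an assumed residual predictor SD of 0.3 to 0.7, adjustment cuts the SE by about 2% to 10% ignoring death and about 1% to 7% with death modelled. With death, that is worth about 2% to 16% more information (1/0.99² = 1.02; 1/0.93² = 1.16), or about 1 to 6 points of power. The rate ratio is essentially unchanged. The true size cannot be read from the document.

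It should not be read as a fault of validity, of the stated event targets, or of precision in the Cox models, where the SE does not fall. The five values are taken as available because eligibility depends on them; completeness of the recorded data is not stated.

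**What to change.** Before database lock, and decided by people without sight of results by arm, prespecify in the analysis plan a fixed list (age, LVEF, NYHA class, haemoglobin, eGFR) alongside treatment and recruitment context in the primary and recurrent-event rate models. Report the context-only model as a sensitivity analysis. Using the same list in the Cox models is optional; if adopted, label those hazard ratios as conditional.

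The cost is a sentence of analysis wording and no new data collection. The small downside is a late change to the primary model in an open-label trial with interim analyses behind it, so the change must be dated and documented as made blind.

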### Treatment

Participants assigned to intravenous iron were administered ferric derisomaltose by infusion at a dose determined by haemoglobin value and body weight (table 1). At each visit, investigators were encouraged to optimise heart failure therapy for both groups, according to contemporary guidelines.

**Table 1 T1:** Intravenous ferric derisomaltose infusion dose regimen

Haemoglobin	Body weight <50 kg*	Body weight 50– <70 kg	Body weight ≥70 kg
≥10 g/dL	20 mg/kg	1000 mg	20 mg/kg up to a maximum of 1500 mg
<10 g/dL	20 mg/kg	20 mg/kg	20 mg/kg up to a maximum of 2000 mg

The dosing table permits an estimation of iron need and utilises a pragmatic approach that takes into consideration a patient’s weight and haemoglobin concentration. Doses up to and including 1000 mg – infused over >15 min. Doses exceeding 1000 mg – infused over 30 min or more.

*At trial design guidance for calculating iron need for this patient group was limited; therefore, a pragmatic administration approach was taken to ensure patients did not receive higher than the maximum licenced dose.

A key goal was to try and ensure that those assigned to intravenous iron were kept iron replete, with redosing with intravenous ferric derisomaltose at the 4-week review and every 4 months after randomisation if either the ferritin was <100 µg/L or, provided ferritin was ≤400 µg/L, TSAT was <25%. If iron deficiency recurred, investigators were encouraged to consider further investigations for potential sources of blood loss. Oral iron supplementation was permitted at the discretion of the investigator in the standard care arm. Any use of non-trial iron supplements was recorded.

The data collected at each timepoint varied, with more in-depth assessment taking place at randomisation, 4 and 20 months (figure 1, online supplemental appendix 1). This included detailed laboratory analysis (local laboratories), 6 min walk test (where possible) and assessments of QoL (Minnesota Living With Heart Failure and EQ-5D).

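### The analysis of covariance for the 10 quality-of-life and 6-minute-walk endpoints omits the baseline value measured at randomisation, which gives up precision although the test stays valid on average

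*Protocol article*

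**What the plan says.** In the protocol article, under Sample size and statistical analysis, "QoL scores and 6 min walk tests results at 4 and 20 months will be compared between randomised treatment groups" and the method is given as "using analysis of covariance, with treatment group and stratification variable as covariates". Nothing in the article says that change from baseline is the outcome.

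Under Treatment, the article describes visits "with more in-depth assessment taking place at randomisation, 4 and 20 months", and the content of those visits includes "6 min walk test (where possible) and assessments of QoL (Minnesota Living With Heart Failure and EQ-5D". Baseline values are therefore collected by design.

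Under Randomisation, the allocation is described as "stratifying by recruitment context (in hospital, recently discharged or ambulatory with elevated natriuretic peptide) and trial site". Both factors are categorical.

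Box 2 puts "Overall Score from Minnesota Living with Heart Failure at 4 months" fourth among the secondary efficacy endpoints. The testing rule is "Endpoints in the list will continue to be tested until one fails to reach 5% significance", and testing starts only if the primary analysis is significant at 5%. The article also says that power was calculated for the first four secondary endpoints, in a supplementary appendix that is not shown. A formal analysis plan is to be finalised before database lock.

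**The concern.** The covariate list is explicit, and it contains no continuous covariate. The baseline value of a quality-of-life score or walk distance is usually its best single predictor at follow-up. Leaving it out means comparing raw follow-up values, adjusted only for how the patient was recruited.

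Two things are lost. The standard error is larger than it needs to be. A chance difference between arms at baseline also stays partly in the treatment estimate.

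The loss matters more here than for a stand-alone secondary endpoint because of the fixed testing order. The overall Minnesota score at 4 months is the first of these endpoints in the sequence. Cardiovascular mortality (5th) and all-cause mortality (9th) come after it.

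**Working it through.** **Step 1. The plan's own figure.** The article says that "570 participants per group (yielding 631 first primary outcomes) would provide 80% power to detect an HR of 0.8 at the 5% significance level". Taking the 5% as two-sided with equal allocation, the Schoenfeld formula gives 4 × (1.960 + 0.842)² / (ln 0.8)² = 631 events, which matches. The same formula at HR 0.75 gives 380, against the stated 379 (power at 379 events is 79.96%). The text shown gives no effect size, standard deviation or power for quality of life or walk distance, so there is no figure of that kind to reproduce.

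**Step 2. Endpoints affected.** In the order of box 2, quality-of-life or walk results at 4 or 20 months stand at positions 4, 6, 7, 12, 13, 14, 15, 16, 19 and 20. That is 10 of 20: four Minnesota, four EQ-5D and two walk-test endpoints. Below position 4 there are 20 − 4 = 16 endpoints.

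**Step 3. Precision.** Let r be the baseline-to-follow-up correlation left after adjustment for the stratification variable. The documents do not give r; 0.3 to 0.7 is assumed.

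- Residual variance with baseline = (1 − r²) × residual variance without it.
- Sample-size factor for the written model = 1 / (1 − r²).
- For an effect with 80% power as written (2.802 standard errors), power with baseline = Φ(2.802 / √(1 − r²) − 1.96).

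| r (assumed) | 1 − r² | Sample-size factor | Power as written | Power with baseline |
|---|---|---|---|---|
| 0.3 | 0.91 | 1.10 | 80% | 83.6% |
| 0.4 | 0.84 | 1.19 | 80% | 86.4% |
| 0.5 | 0.75 | 1.33 | 80% | 89.9% |
| 0.6 | 0.64 | 1.56 | 80% | 93.8% |
| 0.7 | 0.51 | 1.96 | 80% | 97.5% |

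The effect with 80% power as written is 2.802 × √(2/570) = 0.166 SD at 570 per group, or 2.802 × √(2/650) = 0.155 SD at 650 per group. Both ignore deaths and missing scores.

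**Step 4. Simulation check.** With 570 per group, a three-level recruitment context in the model and 3,000 runs per value of r, power without and with baseline was 79% and 83% (r = 0.3), 80% and 89% (0.5), 79% and 94% (0.6), 81% and 98% (0.7). Type I error of the model without baseline was 4.4% to 4.9%.

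**Step 5. Chance imbalance.** Suppose the arms differ at baseline by 1.96 standard errors, with 570 per group. The unadjusted estimate then shifts by r × 1.96 × √(2/570) SD. Given that imbalance, the test statistic under no treatment effect has mean 1.96r and standard deviation √(1 − r²).

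| r (assumed) | Shift in estimate (SD) | Conditional two-sided type I error |
|---|---|---|
| 0.3 | 0.035 | 7.9% |
| 0.5 | 0.058 | 12.9% |
| 0.7 | 0.081 | 20.5% |

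These error rates apply given an unlucky allocation. Over all allocations the rate stays near 5%, as step 4 shows.

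**The case against.** The best defence is that the sentence is shorthand. With only treatment and categorical factors the model would be an analysis of variance, so the name analysis of covariance suggests that a continuous covariate was intended. The article is condensed, and the analysis plan may list the baseline score. This is a fair reason not to claim that the trial will in fact omit baseline. It does not rescue the sentence, which gives a list instead of staying silent and so specifies a model without baseline.

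A second defence is that power may already be adequate. The fourth secondary endpoint had its own power calculation in the appendix not shown. If that used the unadjusted standard deviation, the written model has its planned power and adjustment is a gain on top. For an assumed true effect of 0.25 SD at 570 per group, power as written is about Φ(0.25 × √285 − 1.96) = 99%, and the loss is trivial. This stands: the practical cost depends on an effect size and a correlation that the documents do not give. The correlation may also be weaker at 20 months or for patients assessed in hospital, and recruitment context may absorb a little of the baseline variation.

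A reader might infer that power falls to between 52% and 68%. That takes 80% power with adjustment as the starting point and r of 0.5 to 0.7; the documents support neither. A reader might also infer that a baseline imbalance carries over in full; it carries over multiplied by r. Finally, a reader might infer that the model blocks the mortality endpoints. Testing reaches the Minnesota score only if the primary and the first three secondary endpoints are all significant, and placing that score ahead of mortality is a separate choice.

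**Conclusion.** The point holds as one of efficiency and of conditional bias under chance imbalance. It is not a point about validity: the written analysis keeps its overall error rate, and the primary analysis is untouched. The direction is certain for any non-zero correlation left after adjustment for the stratification variable. The size is not, because it rests entirely on the assumed range of 0.3 to 0.7, and the power gain in step 3 also rests on an effect that just reaches 80% power as written. The consequence is greatest for the overall Minnesota score at 4 months, on the condition that testing gets that far. A change is worth making because the gain costs nothing in data collection.

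**What to change.** State the model for all four Minnesota, four EQ-5D and two walk-test endpoints as analysis of covariance with treatment group, recruitment context and the baseline value of the same measure as covariates. Naming recruitment context also removes an ambiguity: the sentence refers to a single stratification variable, while randomisation used two factors and the trial's other models adjust for recruitment context.

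Add a pre-stated rule for missing baselines, such as mean imputation or a missing-value indicator. The article gives no basis for assuming that few are missing, and the walk test in particular was not expected in every patient.

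If the analysis plan already includes the baseline value, the article's sentence should be corrected to match. The cost is one or two lines of wording before database lock, with no new data.

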**Results:**

Trial recruitment was completed across 70 UK hospital sites in October 2021. Participants were followed until the end of March 2022. We plan to report the results by November 2022.

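### The QoL and 6-minute-walk ANCOVA adjusts for one unnamed stratification variable although randomisation used two; if trial site is the one left out, its standard errors are modestly too large

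*Protocol article*

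**What the plan says.** Under Randomisation, the protocol article describes allocation "stratifying by recruitment context (in hospital, recently discharged or ambulatory with elevated natriuretic peptide) and trial site". It adds that the lists were produced "using a web-based system based on randomised, permuted blocks of variable size". That is two stratification factors, the first with three levels. The abstract's Results paragraph gives 70 sites.

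Under Sample size and statistical analysis, three kinds of model are described:

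- The primary recurrent-event model is fitted "including the randomised treatment group and recruitment context as covariates". For secondary outcomes, "Secondary endpoints involving recurrent events will be analysed as for the primary endpoint".
- The time-to-first-event Cox models contain the treatment effect and recruitment context.
- The ANCOVA for QoL scores and 6-minute walk at 4 and 20 months is fitted "with treatment group and stratification variable as covariates".

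No model names site, and no reason is given for leaving it out. The same section sets a fixed-order test of the secondary endpoints in Box 2 that stops at the first one to miss 5%.

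**The concern.** With two stratification factors, a single stratification variable is not defined. The event models suggest that recruitment context is meant. On that reading the ANCOVA ignores a factor on which the design has already forced balance. Permuted blocks within site keep site differences largely out of the treatment difference, but a linear model without site still counts them as residual noise, so its reported standard error is larger than the true one.

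Walk distance and questionnaire scores are collected locally, so some site variation is plausible, although the article gives no figure for it. Ten of the 20 secondary efficacy endpoints in Box 2 are of this kind: positions 4, 6, 7, 12 to 16, 19 and 20. A narrow miss at position 4 (overall Minnesota score at 4 months) would end formal testing of the 16 endpoints below it, including cardiovascular mortality (position 5) and all-cause mortality (position 9).

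**Working it through.** **The plan's own figures.** The article gives no figure for this point. Its event counts do not depend on site adjustment, and they reproduce. With (1.960 + 0.842)² = 7.849 and 4 × 7.849 / (ln HR)², HR 0.8 gives 31.396 / 0.04979 = 631 and HR 0.75 gives 31.396 / 0.08276 = 379.4, against 631 and 379 stated.

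**Layout.** 650 per group is 1,300 participants. Over 70 sites that is 1,300 / 70 = 18.6 per site, and over 70 × 3 = 210 site-by-context cells it is 6.2 per cell.

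**Theory for the linear model.** Let ICC be the share of outcome variance, after treatment and context, that lies between sites. Take total variance as 1 and N participants allocated 1:1.

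- SE reported without site: 2/√N.
- True SE when arms are balanced within site: 2√(1 − ICC)/√N.
- Ratio: 1/√(1 − ICC).

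For N = 1,140 (570 per group) the first is 2/√1,140 = 0.0592. At ICC 0.10 the second is 0.0592 × √0.90 = 0.0562.

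**Simulation.** Real blocks are often incomplete and site effects must be estimated, so the theory was checked by simulation with 70 unequal sites and permuted blocks within site-by-context cells. Site sizes, context mix and ICCs are assumptions. Entries are the context-only SE divided by the SE with site in the model.

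| Assumed ICC | Theory | Random intercept, N = 1,000 (1,000 runs) | Random intercept, N = 1,140 (200 runs) | Fixed site terms, N = 1,000 |
|---|---|---|---|---|
| 0 | 1.000 | 1.00 | not run | 0.99 |
| 0.02 | 1.010 | 1.01 | 1.009 | 1.00 |
| 0.05 | 1.026 | 1.02 | 1.024 | 1.01 |
| 0.10 | 1.054 | 1.05 | 1.052 | 1.04 |

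The random intercept recovers nearly all of the theoretical gain. Fixed site terms recover less, and lose slightly at ICC 0. In the N = 1,000 random-intercept runs, rejection under no treatment effect was 4% to 6% in both models.

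**What the ratio means.** A ratio r is equivalent to discarding 1 − 1/r² of participants: 2.0% at r = 1.01, 3.9% at 1.02 and 9.3% at 1.05. As an illustration, take an endpoint whose test would have 80% power with the correct SE. Its power with the inflated SE is Φ(2.802 − 1.960r): 79.4%, 78.9% and 77.1%.

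**Event models.** The same reasoning does not carry over.

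- Cox, true HR 0.75, about 390 to 420 events: the context-only SE was smaller than the site-stratified SE, 0.1025 against 0.1054 with no site effect and 0.0987 against 0.1018 at a site log-hazard SD of 0.6. The cost of omission was a small pull toward 1 (HR 0.765 against 0.752 at SD 0.6).
- Recurrent events, proportional-rates model: adding pooled-site strata left the sampling SD of the estimate unchanged within simulation error, 0.125 against 0.126 (site log-SD 0.3) and 0.133 against 0.132 (0.5).
- Recurrent events, Poisson model with robust variance as a stand-in: the context-only SE was 1.02 to 1.08 times the SE with site terms. The 1.02 arose with no site effect at all, because many site terms bias the robust SE downward.

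**The case against.** The strongest reply is that leaving out a 70-level factor is common and defensible. There are about 19 participants per site, and the revised target of 379 first events is 379 / 70 = 5.4 per site. Omission errs on the conservative side, and no ICC is given, so the loss could be nil. With fixed site terms there is no gain at ICC 0.02 and a small loss below it. A formal analysis plan was still to be finalised, and the article is condensed.

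Much of this stands. It makes the point minor and settles the matter for the event models. It does not dispose of the ANCOVA. The article states the covariates, and what it states is undefined against its own randomisation scheme, so this is not merely detail deferred. The loss from fixed site terms does not apply to a random intercept, which showed no loss at ICC 0.

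A reader might go further and infer that every planned model adjusts for recruitment context alone and that all intervals, including the primary one, are too wide. The article does not support this. The ANCOVA sentence does not name recruitment context; that it is meant is an inference from the other models. Cox intervals are not wider without site, and the primary model showed no measurable gain from pooled-site strata. The error-term argument belongs to the linear models only.

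**Conclusion.** The point holds for the ten continuous QoL and walk endpoints and is minor. The stated ANCOVA covariate is ambiguous. If it means recruitment context, standard errors are too large by about 1%, 2% and 5% at assumed site ICCs of 0.02, 0.05 and 0.10, with no difference at 0.

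This rests on three assumptions: that reading of the term, the assumed ICCs and site sizes, and blocks that balance the arms closely within site. If a baseline score is also fitted, the relevant ICC is the one that remains after baseline adjustment, which may be smaller. If the term was meant to cover both factors, only the wording needs correcting.

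It would be wrong to infer that the trial's tests are anti-conservative or its sample size miscalculated. Omitting site does not inflate type I error, and both event counts reproduce.

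**What to change.** In the analysis plan, replace the undefined term in the ANCOVA for the ten QoL and 6-minute-walk endpoints with both factors by name: recruitment context as a fixed factor and trial site as a random intercept. State that if the site variance is estimated as zero, the model reduces to one with recruitment context alone.

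Leave the primary rate model and the Cox models as planned. A sentence explaining why site is left out of them would help. A site-stratified analysis there is optional and should be labelled supportive.

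The cost is a change of wording and slightly more analysis work. Site is already recorded for every participant because it was used at randomisation, so no new data are needed.
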